### Trial design {8}

The GOAL Trial is a pragmatic, multicentre, superiority, open-label cluster randomised controlled trial. While the intervention will be implemented at the participant level, randomisation at the cluster (hospital) level has been chosen to avoid contamination of the intervention. The Australasian Kidney Trials Network (AKTN, The University of Queensland) is the sponsor and coordinating centre for the trial.

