### Sample size {14}

Based on data from community-dwelling frail older adults, it is estimated that CGA will improve the GAS score by at least 10 points from an average score of 36 at baseline (which presents a change in one standard deviation, equivalent to a medium effect size) [25].

It is estimated that a cluster randomised trial with an average cluster size of 20 participants (coefficient of variation of sizes = 1) would require 16 hospital sites (clusters) with 8 sites in the intervention and control arm, respectively, to achieve 90% power to detect a mean difference in GAS score of 10 units at 3 months follow-up. This power calculation, giving a sample size of 320, assumes a common standard deviation of 10 units and an intra-cluster correlation coefficient of 0.3. To achieve sufficient power for the analysis of the secondary outcome of GAS at 12 months, an allowance for a 33% loss to follow-up over the 12 months was included, requiring baseline GAS observations from 478 participants. The 16 sites will be expected to each have a minimum of 55 patients who meet the eligibility criteria. Based on previous studies, it is estimated that approximately 10% of eligible patients will not consent to participate [26, 29] and a further 35% will not meet the frailty criteria [38] leaving a recruitment target of 500 (approximately 30 at each site). Assumptions in the sample size calculation will be re-estimated on trial data at the mid-point of the planned recruitment period.

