## Statistical methods

### Statistical methods for primary and secondary outcomes {20a}

Data will be analysed at the individual patient level. The primary outcome, Goal Attainment Scaling (GAS) scores at three months, will be analysed using a linear regression model with the intervention group as a binary covariate and baseline GAS score as a continuous covariate. To allow for the clustering of data within study centres, inference will be based on robust standard errors. Multiple imputation will be used if there is more than 5% missing data on the three-month GAS scores. Subgroup analysis of GAS scores at three months will be undertaken based on baseline characteristics of patients (including age, CKD stage, and frailty status) and study site (including unit size). Subgroup effects will be assessed via treatment-by-subgroup interactions in linear regression models.

Repeatedly measured continuous secondary outcomes (GAS scores at 6 and 12 months, EQ-5D-5L scores, FI) will be analysed using mixed models for repeated measures (MMRM) with a random intercept for the study centres and an unstructured variance–covariance matrix to model the within-patient correlation structure due to the repeated measurements. The models will have fixed effects for the intervention group, categorical time, the intervention-by-time interaction, and baseline measurements of the outcome. The primary results will be the treatment effect estimates at 6 and 12 months and 95% confidence limits.

Other secondary outcomes will be analysed using regression models appropriate for the type of outcome. The effect of CGA on the rate of hospital admission will be tested using a Poisson regression model with a random intercept for study centres and the effect of CGA on time to all-cause mortality and time to hospital admission will be assessed using Cox regression with frailty (random intercepts) for study centres. A detailed statistical analysis plan will be made public before unblinding of the trial statistician and other study personnel at the coordinating centre.

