#### Cost-effectiveness evaluation

For the assessment of cost-effectiveness, a cost-utility analysis will be undertaken with the primary analysis from the perspective of the healthcare system. An incremental cost-effectiveness ratio (CER) per quality adjusted life years (QALY) gained in the intervention arm, compared with the usual care arm, will be calculated following the formula:$$\mathrm{CER}=\frac{{\mathrm{Cost}}_{\mathrm{int}}-{\mathrm{Cost}}_{\mathrm{cont}}}{{\mathrm{QALY}}_{\mathrm{int}}-{\mathrm{QALY}}_{\mathrm{cont}}}$$where int = intervention group (receiving CGA) and cont = control group (receiving usual care).

Cost of the intervention will be calculated based on additional time over usual care for the nurse and geriatrician to complete their assessments. Costs specific to the research (e.g. research assessments) will not be included. Cost of health care usage in the intervention and control group will be calculated from diaries filled out by participants and from hospital records where available. Unit costs of care will be derived from appropriate sources for the care. For primary care, the Medicare schedule with out of pocket will be applied and average Australian Refined Diagnosis Related Groups (AR-DRG) applied for hospital stays. Other costs will be applied at appropriate wage standards for the care provided.

Utility scores will be derived from the EQ-5D-5L [62] using the Australian algorithm if available (unpublished) or the UK algorithm [63]. Quality-adjusted life years for each group will be calculated using the utility score multiplied by time in the study.

Sensitivity analyses will be conducted for cost variations, intervention durations, as well as EQ-5D-5L score variations. Additional analyses will be conducted should there exist cluster effect and variation across sub-groups (e.g. study location, gender, age, frail levels and other relevant comorbidities). Reporting of the cost-utility analysis will follow the Consolidated Health Economic Evaluation Reporting Standards (CHEERS) guideline [64].

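### The cost-utility analysis allows for clustering only if a cluster effect turns up, and then only as an additional analysis, although hospitals are randomised

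*Protocol article*

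**What the plan says.** All references are to the protocol article.

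- **Trial design {8}:** the intervention is delivered to individuals, but "randomisation at the cluster (hospital) level has been chosen to avoid contamination of the intervention".
- **Cost-effectiveness evaluation, base case:** "An incremental cost-effectiveness ratio (CER) per quality adjusted life years (QALY) gained in the intervention arm, compared with the usual care arm, will be calculated". The formula that follows divides the difference in arm costs by the difference in arm QALYs. No cluster term and no interval method accompany it.
- **Same section, sensitivity analyses:** "Sensitivity analyses will be conducted for cost variations, intervention durations, as well as EQ-5D-5L score variations". Clustering is not on this list.
- **Same section, clustering:** its only appearance is "Additional analyses will be conducted should there exist cluster effect and variation across sub-groups". The sentence goes on to list examples such as location, gender, age and frailty level.
- **Statistical methods {20a}:** the clinical analyses carry no such condition. For the primary outcome, "To allow for the clustering of data within study centres, inference will be based on robust standard errors". Repeated continuous outcomes, EQ-5D-5L among them, use "mixed models for repeated measures (MMRM) with a random intercept for the study centres". The admission rate uses a "Poisson regression model with a random intercept for study centres".
- **Sample size {14}:** the calculation assumes "an intra-cluster correlation coefficient of 0.3" for GAS.

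**The concern.** In a cluster-randomised trial, patients at one hospital share an allocation and may share practice patterns. The variance of an arm difference therefore includes a between-hospital part whether or not that part can be shown to differ from zero. The cost-utility text sets two hurdles. Clustering is considered only if an effect exists, and what follows is only an additional analysis, placed beside subgroup variation.

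This is at odds with the rest of the plan. EQ-5D-5L supplies the utilities and admissions are a component of cost. Both are modelled with a centre effect unconditionally, but the quantities derived from them are not.

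The stake is the stated uncertainty around incremental costs, incremental QALYs and their ratio. Cost-effectiveness is a secondary objective, and the Discussion part of the abstract ties adoption into routine practice to clinical and cost-effectiveness.

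**Working it through.** **1. The plan's own clustered figure.** No figure is given for the cost-utility analysis. The only one to reproduce is the 90% power for GAS, from Sample size {14}: 8 sites per arm, mean size m = 20, CV of sizes 1, SD 10, difference 10, ICC 0.3. A two-sided 5% level is assumed.

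- Equal-size design effect: 1 + (20 − 1) × 0.3 = 6.7.
- Relative efficiency for unequal sizes: 1 − CV² × L(1 − L), with L = 20 × 0.3 / (20 × 0.3 + 0.7) = 0.896, giving 0.906.
- Design effect: 6.7 / 0.906 = 7.39. Effective n per arm: 160 / 7.39 = 21.65.
- SE = 10 × √(2 / 21.65) = 3.04. Power = Φ(10 / 3.04 − 1.96) = 0.908.

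This agrees with 90%. The plan therefore treats clustering as a design feature when it sizes the trial.

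**2. Inputs for the cost-utility analysis.** There are 16 sites. Recruitment is about 30 per site, and after the 33% loss allowed over 12 months about 30 × 0.67 = 20 remain, so m = 20 and m = 30 bracket the analysis. The ICC for costs and QALYs is not given; 0.01 to 0.10 is assumed. Site sizes are taken as equal or with the plan's CV of 1.

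**3. If the base case is never adjusted.** For a difference of unweighted patient means, the design effect is DE = 1 + ((1 + CV²)m − 1) × ICC. The true size of a nominal 5% test is 2 × (1 − Φ(1.96 / √DE)).

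| m | ICC | DE, equal | True size | DE, CV 1 | True size |
|---|---|---|---|---|---|
| 20 | 0.01 | 1.19 | 7.2% | 1.39 | 9.6% |
| 20 | 0.05 | 1.95 | 16.0% | 2.95 | 25.4% |
| 20 | 0.10 | 2.90 | 25.0% | 4.90 | 37.6% |
| 30 | 0.01 | 1.29 | 8.4% | 1.59 | 12.0% |
| 30 | 0.05 | 2.45 | 21.0% | 3.95 | 32.4% |
| 30 | 0.10 | 3.90 | 32.1% | 6.90 | 45.6% |

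Simulation with unequal sizes drawn at CV 1 gives a slightly lower range, 8.6% to 41.5%. Taking formula and simulation together, the range is about 7–32% (equal) and about 9–46% (CV 1).

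**4. If an adjusted result replaces the base case after a significant test.** The article names no test, so a 5% F test for centre within arms is assumed. It is followed by a cluster-level t test on 14 degrees of freedom if significant, and by the unadjusted test otherwise. With equal sizes:

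| m | ICC | Chance of detecting the ICC | Size, test first | Size, always clustered |
|---|---|---|---|---|
| 20 | 0.01 | 14% | 6.3% | 4.9% |
| 20 | 0.02 | 26% | 7.6% | 5.1% |
| 20 | 0.05 | 63% | 7.6% | 5.0% |
| 20 | 0.10 | 91% | 5.9% | 5.0% |
| 30 | 0.01 | 19% | 7.1% | 5.3% |
| 30 | 0.02 | 39% | 7.5% | 4.7% |
| 30 | 0.05 | 81% | 6.6% | 4.9% |
| 30 | 0.10 | 98% | 5.3% | 5.1% |

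With CV 1 the test-first size is about 7–12%. Its low end depends on how the unequal sizes are drawn: one set gave 6.2% at ICC 0.10 with 30 per site.

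**The case against.** The strongest reply is that the section gives a point-estimate formula and nothing else. It contains no standard error, bootstrap or test, and the formula itself assumes no independence. A reader might infer that the trial's default intervals will treat patients as independent and so be too narrow. The document does not say that, and an article may leave the interval method to the analysis plan. This stands, and it is why the size is conditional. It does not remove the point, because the article states a conditional rule and an analysis plan that follows it would inherit it.

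A reader might also take the never-adjusted figures as the size of the defect. They apply only if the adjusted result stays secondary. The text does not say whether it would replace the base case; if it did, most of the excess disappears.

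Nor is it right that 16 sites can rarely reveal a cluster effect. Detection is poor at ICC 0.01 to 0.02 (14–39%), but 63–81% at 0.05 and 91–98% at 0.10 with equal sizes.

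The GAS ICC of 0.3 cannot be carried over to costs or QALYs. Valuing care by the Medicare schedule and average AR-DRG costs also removes some between-hospital price variation, though not variation in use.

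Finally, the sentence could be read as a plan to explore heterogeneity between sites. On that reading the section says nothing about clustering in the base case, and the wording still needs separating.

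**Conclusion.** The point holds as a flaw in the stated rule. Allowance for clustering in the cost-utility analysis is conditional and merely additional, in a trial that randomises hospitals and allows for centre unconditionally in the outcomes that feed this analysis.

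Its size depends on how the sentence is applied and on ICCs the document does not give. Under ICCs of 0.01–0.10 and 20–30 patients per site, a nominal 5% test would run at:

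- about 7–32% (equal sizes) or 9–46% (CV 1) if the base case is never adjusted;
- about 5–8% (equal sizes) or 7–12% (CV 1) if adjustment replaces the base case after a significant cluster test.

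The excess vanishes only if the true ICC is zero, or nearly so when a large ICC is reliably detected. The point estimate of the ratio as defined is not in question, and neither are the clinical analyses. The change is worth making because it is cheap and concerns a secondary objective with policy weight.

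**What to change.** In Cost-effectiveness evaluation:

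1. Delete the condition that a cluster effect must exist.
2. State that uncertainty around incremental costs, incremental QALYs and the ratio allows for centre in the base case, whatever cluster effect is observed. A multilevel model for costs and QALYs, or a bootstrap that resamples centres, would do this; the choice can be left to the analysis plan.
3. Keep variation across subgroups as a separate analysis in its own sentence.

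The cost is a wording change, modest extra analysis work and wider intervals. The design and data collection are unaffected.

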#### Process evaluation

For the process evaluation, descriptive statistical methods will be used to summarise the details of the process of trial performance and CGA delivery, as well as issues noted, including the number and percentages of issues noted in each of the sites, and will also be analysed qualitatively by summarising them in themes, if such themes emerge. The patient and health professional qualitative interviews will be analysed using a thematic framework approach, by extracting themes from the interview transcripts, supported by software (NVivo).

### Interim analyses {21b}

No interim analyses are planned for outcomes. As noted elsewhere, an interim analysis of the sample size is planned.

### Methods for additional analyses (e.g. subgroup analyses) {20b}

Subgroup analysis may be undertaken based on participant (age, CKD stage, frailty) and study site (region, size) characteristics where possible.

### Methods in analysis to handle protocol non-adherence and any statistical methods to handle missing data {20c}

Protocol deviations (e.g. delayed CGA, cross-over) will be investigated in sensitivity analyses. Imputation of randomly missing values will be tested during sensitivity analyses.

### Plans to give access to the full protocol, participant level-data and statistical code {31c}

Access will only be provided after the primary results of the trial and any pre-specified analyses are published. De-identified individual participant data will be made available upon request to a Data Access Committee, a review board set up to assess proposals based on sound science, benefit-risk balancing and research team expertise. Appropriate data will be made available to approved proposals. This process will be in effect for a period of up to 5 years following the publication of the main study results. After 5 years, the data will be available in the Sponsor’s data warehouse but without investigator support other than deposited metadata.

## Oversight and monitoring

### Composition of the coordinating centre and trial steering committee {5d}

The Australasian Kidney Trials Network (AKTN) is the coordinating centre on behalf of the University of Queensland. As the Central Coordinating Centre it is tasked with responsibilities including site set-up and close-out, training, monitoring, data management, statistics, distributions of funds to sites, and supporting the central operations including governance and committees.

The Trial Steering Committee (TSC) is comprised of persons appointed through AKTN procedures, including chief investigators, a statistician and consumers. It is chaired by the Chief Principal Investigator. It is the responsibility of this group to provide leadership to the overall conduct of the trial and ensure trial integrity. In particular, this group will review the progress of the study in achieving the objectives, take appropriate decisions to meet these objectives and make decisions regarding the continuation or modification of the trial given reports from the Data and Safety Monitoring Board. The TSC oversees the trial-related activities of the coordinating centre, AKTN, and reports to the AKTN Scientific Committee.

The Trial Management Committee (TMC) comprises selected chief investigators including the Chair of the TSC, AKTN executive committee member, clinical operations manager, clinical project manager, clinical research associates, statisticians, data managers, and a PhD candidate. The TMC provides support to the TSC in the execution of their responsibilities. Its focus is primarily on operational matters regarding the trial’s management and conduct. It provides regular reports to the TSC with information including site status, recruitment, retention, protocol compliance, data completeness and legal and regulatory issues.

The Consumer Advisory Board comprises nine consumers and a PhD candidate. They provide input on trial design and implementation, and the dissemination of findings, and reports to both the TSC and the TMC. Two consumers are also members of the TSC.

### Composition of the data monitoring committee, its role and reporting structure {21a}

An independent Data and Safety Monitoring Board (DSMB) will monitor safety data, data integrity and trial conduct, and review unblinded data on the incidence and circumstances of safety outcomes. It will be comprised of a nephrologist, a geriatrician and a statistician, all of whom have no financial or scientific conflicts of interest with The GOAL Trial. The DSMB will report to the Chair of the TSC and also the Chair of the AKTN Executive Operations Secretariat.

### Adverse event reporting and harms {22}

No serious adverse events are anticipated to occur as a result of the CGA intervention or assessments (e.g. FI, GAS, EQ-5D-5L) in this trial. Adverse events, such as injurious falls, cardiac events, medication side effects, or death, will be captured by data collected for the secondary outcomes of mortality and hospitalisations. The Data and Safety Monitoring Board will look at trends between the control and intervention groups and action as appropriate.

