**Methods:**

The GOAL Trial is a pragmatic, multi-centre, open-label, superiority, cluster randomised controlled trial developed by consumers, clinicians, and researchers. It has a two-arm design, CGA compared with standard care, with 1:1 allocation of a total of 16 clusters. Within each cluster, study participants ≥ 65 years of age (or ≥ 55 years if Aboriginal or Torres Strait Islander (First Nations Australians)) with CKD stage 3–5/5D who are frail, measured by a Frailty Index (FI) of > 0.25, are recruited. Participants in intervention clusters receive a CGA by a geriatrician to identify medical, social, and functional needs, optimise medication prescribing, and arrange multidisciplinary referral if required. Those in standard care clusters receive usual care. The primary outcome is attainment of self-identified goals assessed by standardised Goal Attainment Scaling (GAS) at 3 months. Secondary outcomes include GAS at 6 and 12 months, quality of life (EQ-5D-5L), frailty (Frailty Index – Short Form), transfer to residential aged care facilities, cost-effectiveness, and safety (cause-specific hospitalisations, mortality). A process evaluation will be conducted in parallel with the trial including whether the intervention was delivered as intended, any issue or local barriers to intervention delivery, and perceptions of the intervention by participants. The trial has 90% power to detect a clinically meaningful mean difference in GAS of 10 units.

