GPs often have insights into patients’ functional and cognitive problems that are not recognised or documented by hospital-based teams. The patient’s GP will be asked to consider making a referral to the geriatric outpatient clinic as per routine practice and asked to provide any additional relevant information that they feel would be relevant. This will occur once a participant is enrolled, and before they are seen in the outpatient clinic by the Geriatrician.

Following the CGA, the geriatrician will generate a letter to the treating nephrologist, GP and any other relevant specialists, which will include a comprehensive problem list and recommendations regarding an individualised care plan. The necessary referrals to allied health professionals and other specialists will be undertaken by the treating geriatrician where the site has their own Day Hospital or relevant outpatient service. Where such services are not available, the letter will request the assistance of the participant’s GP to make the required referrals to community-based providers.

The CGA intervention concludes once the geriatrician issues their letter and makes the referrals. It does not extend to ensuring a participant’s compliance with the recommendations, the GP actioning recommended medication changes, or a participant’s attendance at any referred allied health interventions.

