**Safety objective**		
To determine whether CGA is safe when administered to frail older patients with stages 3–5/5D CKD	Any associated hospital admissions or mortality	Continuous

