#### Safety

Data collected for the secondary outcomes related to mortality and associated hospital admissions will be used for monitoring participant safety.

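### Falls and medication side effects are said to be captured by the mortality and hospitalisation data, but those data hold only the events that lead to admission or death, so the safety conclusion must be limited to these

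*Protocol article*

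**What the plan says.** Item {22} gives four examples of adverse events and, in the same sentence, states how they will be found: "injurious falls, cardiac events, medication side effects, or death, will be captured by data collected for the secondary outcomes of mortality and hospitalisations". It adds that the DSMB will compare trends between the arms and that no serious adverse events are expected from the intervention.

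Three other places name the same data source. The Safety paragraph under {18a} reads: "Data collected for the secondary outcomes related to mortality and associated hospital admissions will be used for monitoring participant safety". In Table 2 the safety objective is "To determine whether CGA is safe when administered to frail older patients", and its outcome measure is "Any associated hospital admissions or mortality". The abstract lists cause-specific admissions and deaths as the safety outcomes. The secondary hypotheses in Objectives {7} include, without qualification, that comprehensive geriatric assessment (CGA) is safe.

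According to the abstract, the geriatrician's assessment is meant to "optimise medication prescribing, and arrange multidisciplinary referral if required". Under {11a} the intervention ends with the letter and referrals, and does not extend to "the GP actioning recommended medication changes".

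**The concern.** Item {22} is a positive statement about ascertainment, so this is not a detail that a condensed article has left to the full protocol or the analysis plan. The statement is true for deaths, and for any fall, cardiac event or drug reaction that results in an admission. It is not true for a fall treated without admission, or for a side effect dealt with by changing a prescription.

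This matters for this particular intervention. Medication review and mobility, balance and falls are among the CGA components in Table 1, and {11a} leaves the recommended medication changes to the GP. Some of the consequences, good or bad, will therefore arise in primary care and never reach a hospital admission record. A reader who takes {22} at its word would accept a similar number of admissions and deaths in the two arms as evidence that falls and side effects were also similar. The data would not show that.

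**Working it through.** The article gives no safety figure to reproduce. The check sets the passages side by side and follows each named event through the stated route.

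1. **Events named in {22}:** injurious falls, cardiac events, medication side effects and death, given as examples.

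2. **Designated safety sources:**
   - Abstract: cause-specific hospitalisations and mortality.
   - Table 2, safety row: associated admissions or mortality.
   - {18a}, Safety: mortality and associated admissions.
   - {22}: the mortality and hospitalisation outcomes.

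   All four agree, and none names another source.

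3. **Each event through that route:**
   - Death: captured.
   - Fall, cardiac event or side effect with admission: captured, and Table 2 records the number of admissions and the reason.
   - Fall, cardiac event or side effect with neither admission nor death: not in the designated safety data.

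4. **Other data described in the article:**
   - The Health Care Diary is assigned to costing (Health care use analysis) and to a comparison of service counts with data linkage (Patient recall of health service utilisation).
   - EQ-5D-5L, the Frailty Index and Goal Attainment Scaling are efficacy measures.
   - Any of these may carry an indirect trace of harm, but none is designated as safety data.

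5. **Size of the gap:** let s be the share of injurious falls and medication side effects that lead to admission or death. The route captures s and misses 1 - s. The documents give no value for s, so the following values are assumptions only:
   - s = 0.1: 1 - 0.1 = 0.9, so 90% missed.
   - s = 0.3: 1 - 0.3 = 0.7, so 70% missed.
   - s = 0.5: 1 - 0.5 = 0.5, so 50% missed.
   - s = 1: nothing missed. This is the only value at which {22} is correct as written.

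6. **What could still be collected:** under Trial status, enrolment began on 15 March 2021 and was due to end on 1 July 2023, about 27.5 months. The article appeared on 30 May 2023. Anyone enrolled before 30 May 2022 had by then passed 12 months. That covers the first 14.5 months or so of the recruitment window (15 March 2021 to 30 May 2022). Questions added at that point would miss those participants altogether and would miss earlier contacts for many of the rest.

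**The case against.** The strongest reply is that the limit is already disclosed. The safety row of Table 2 names admissions and mortality as its outcome measure, and the abstract and the Safety paragraph agree. On that view only one loosely worded sentence in {22} is at fault. Much of this stands, and it is why the fix is mainly wording. It does not remove the point: {22} still claims capture of events that the route cannot see, and the hypothesis in {7} and the objective in Table 2 still speak of safety without restriction.

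A second reply is that admissions and deaths are a defensible choice for a pragmatic, open-label trial judged to be of low risk. Participants know their allocation, and CGA itself deals with falls and medicines, so asking about these events could raise reporting in the intervention arm alone. This stands as a reason not to insist on new questions.

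Three stronger readings are tempting, and the documents do not support them:

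- A reader might infer that the trial cannot judge the main risks of CGA. The article ranks no risk as the main one and anticipates no serious adverse events from CGA. Harms leading to admission are recorded with their reason, and the DSMB reviews unblinded safety outcomes ({21a}). Serious harm can therefore be compared between arms.
- A reader might infer that most of the named events are lost. That depends on s, which is not given, and death, one of the four examples, is fully captured.
- A reader might infer that nothing is asked about harms at the follow-up contacts. The schedule figure, the case report forms and the diary form are not shown. All that can be said is that the article describes no such collection.

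**Conclusion.** The concern holds in a limited form. By the article's own account, safety rests on hospital admissions and deaths alone. Item {22} therefore overstates capture of injurious falls and medication side effects, and the trial can draw a safety conclusion only about harms that lead to admission or death. This follows from the text and needs no assumption about event rates. The share missed, 1 - s, cannot be estimated from the documents. The percentages in the working illustrate the relation and do not estimate it. The point is worth correcting because it changes what the trial may conclude about safety. It does not affect the primary outcome or the comparison of serious harms.

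**What to change.** - **Reword {22}** to say that adverse events are captured only where they lead to hospital admission or death, and that falls and medication side effects managed without admission are not part of the safety data.
- **Limit the safety hypothesis in Objectives {7}, the safety objective in Table 2 and the eventual conclusion** to hospitalised or fatal harms. These two changes are text only and can be made at any stage.
- **Use the diary where it allows.** If the Health Care Diary form already records emergency and GP contacts, tabulate them by arm for the DSMB and the final report as descriptive supporting data. State that they are unblinded self-report and may be reported differently in the two arms. The cost is one additional table.
- **Optional:** ask the same short questions on injurious falls and medication side effects in both arms at the remaining 3-, 6- and 12-month contacts. This adds a little time per contact, covers only part of follow-up given the recruitment dates, and is open to arm-specific reporting. It would support the rewording but could not replace it.
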